## Abstract

**Aims:**

Lifestyle modification, including caloric restriction and exercise, is fundamental in the treatment of people living with overweight and type 2 diabetes mellitus (T2D). The overall aim of lifestyle intervention schemes is to reduce body weight and improve glycaemic control to reduce the future risk of diabetes‐associated complications. The aim of this study is to determine whether intermittent energy restriction, exercise or their combination is best suited for reaching these targets in individuals with T2D not treated with insulin.

**Methods:**

This randomized, controlled, monocentric parallel‐group trial is designed to investigate participants living with T2D, body mass index >27 kg/m^2^, HbA1c ≥53 mmol/mol (≥7.0%) and ≤86 mmol/mol (≤10.0%) and without insulin therapy. Participants are equally and randomly allocated to one of four study groups: (1) intermittent energy restriction group, (2) exercise group, (3) combined intermittent energy restriction and exercise group and (4) control group. The intervention phase lasts 12 weeks, followed by a two‐year follow‐up phase. In addition to assessing body weight and glycaemic parameters, resting energy expenditure (REE) and body composition are measured. An oral glucose tolerance test is carried out at baseline and at the end of the intervention. Additionally, stool samples for microbiome analyses and individual‐related outcomes are collected, and all participants are equipped with continuous glucose monitoring (CGM). The primary outcome measure is the change in bodyweight from baseline to day 84.

**Trial Registration:**

The study was registered at DRKS (Deutsches Register Klinischer Studien—German Clinical Trial Register DRKS‐ID: DRKS00032036)—Date of registration: 11.10.2023.

What's new?
Lifestyle intervention is a cornerstone of therapy for type 2 diabetes mellitus (T2D), aiming to improve glucose metabolism and reduce body weight.Intermittent energy restriction was proven to be a safe and effective method to improve glycaemic control and body weight.Comparative effectiveness trials of intermittent energy restriction and regular physical activity or a combination of both in people with T2D are scarce.The INTERFAST‐3 study aimed to determine whether intermittent energy restriction, exercise or their combination is best suited for reducing bodyweight and improving glucose metabolism in individuals with T2D.

## INTRODUCTION

1

Type 2 diabetes mellitus (T2D) is a chronic metabolic disorder characterized by persistent hyperglycaemia due to a progressive loss of β‐cell insulin secretion commonly on the background of insulin resistance.^1^, ^2^ The International Diabetes Federation (IDF)^3^ estimates the prevalence of diabetes in 2024 at approximately 590 million adults, which provides to be a global burden on public health and projections suggest that the number of people with diabetes could rise beyond 850 million until 2050.^3^ T2D causes undesirable health consequences in multiple areas of the human body such as increasing the incidence of serious disorders affecting eyes, kidneys, somatic nerves, autonomic nerves, feet, heart,^4^, ^5^ brain, blood vessels, liver, skeleton and other tissues.^3^, ^6^, ^7^, ^8^

Overweight and obesity represent a multifactorial disease in which, besides genetic predisposition, exposure to an environment characterized by sedentary behaviour and high‐calorie intake contributes as a significant risk factor for the development of T2D.^9^, ^10^ The excessive free fatty acid release by adipose tissue leads to a decrease in insulin sensitivity of muscles, adipose tissue and liver, followed by increased glucose levels, insulin resistance and T2D.^11^, ^12^, ^13^, ^14^

As a result, institutions such as the ADA (American Diabetes Association) or the WHO (World Health Organization) recommend body weight reduction through calorie restriction, along with at least 150 min of moderate‐intensity aerobic physical activity or 75 min of vigorous‐intensity aerobic physical activity spread over at least 3 days per week.^15^, ^16^

Dietary modifications aiming to reduce body weight represent one cornerstone of treatment of people living with obesity and type 2 diabetes for blood glucose, weight and cardiovascular risk‐factor management.^17^ Intermittent energy restriction (IER), defined as periods of caloric restriction alternating with periods of ad libitum eating has been proposed as an umbrella term including intermittent fasting and time‐restricted eating.^18^ While previous data has demonstrated that IER regimens have similar effects on anthropometric and cardiometabolic risk factors^19^ current diabetes guidelines highlight the simplicity of IER for people looking for a practical dietary weight loss tool, who are challenged by continuous caloric restriction regimens.^20^

Although previous studies have demonstrated beneficial effects of dietary restrictions and exercise individually in people with T2D, data on the combined impact of an IER regimen and physical activity compared with each lifestyle intervention alone remains scarce.^21^ Understanding the interaction between exercise and intermittent energy restriction is therefore crucial in order to find the best lifestyle intervention strategies. Hence, the aim of this ongoing study is to assess the safety and efficacy of IER, structured exercise and their combination in people living with overweight/obesity and T2D.

## METHODS

2

### Study hypothesis

2.1

Caloric restriction and exercise are keystones of anti‐hyperglycaemic therapy. We hypothesize that the combination of both interventions is safe and most effective for bodyweight reduction and HbA1c lowering in people living with overweight and T2D (Figure 1).

**FIGURE 1 dme70328-fig-0001:**
[figure not shown]
Study overview.

### Study design

2.2

This randomized, controlled, parallel‐arm trial is designed to compare the effects of intermittent energy restriction, structured exercise and their combination in people living with overweight/obesity and T2D. The study visits take place at the Cardiometabolic Trials Unit at the Medical University of Graz (Table 1).

**TABLE 1 dme70328-tbl-0001:** Visit schedule.

	Visit 1 (−14 to 3 days)	Visit 2 Baseline	Visit 3 (28 ± 7 days)	Visit 4 (56 ± 7 days)	Visit 5 (84 ± 7 days)	Visit 6 (184 ± 14 days)	Visit 7 (365 ± 14 days)	Visit 8 (730 ± 21 days)
Informed consent	X							
Inclusion/exclusion criteria	X							
Randomization		X						
Demography, medical history	X							
Concomitant medication	X	X	X	X	X	X	X	X
Vital signs	X	X	X	X	X	X	X	X
Height	X							
Weight	X	X	X	X	X	X	X	X
Physical examination	X				X			
Electrocardiography (ECG)	X							
Resting energy expenditure (REE)		X			X			
Blood sampling		X	X	X	X	X	X	X
Biobanking		X	X	X	X	X	X	X
Oral glucose tolerance test		X			X			
Adverse events			X	X	X	X	X	X
Bioelectrical impedance analysis		X	X	X	X	X	X	X
6‐min walk test (6‐MWT)		X			X			
Food frequency questionnaire (FFQ)		X	X	X	X	X		
International physical activity questionnaire (IPAQ)		X	X	X	X	X		
Start of CGM use		X						
End of CGM use					X			
Lifestyle counselling		X			X			
Eating disorder examination (EDE‐Q)		X	X	X	X	X		
Sleep quality questionnaire		X	X	X	X	X		
Food craving inventory		X	X	X	X			
Beck depression questionnaire (BDI)		X	X	X	X			
Application/removal movisens		X	X	X	X			
Faeces sampling		X			X			
Whole blood aggregation		X	X	X	X			
Heart rate monitoring^*^		X						
Removal heart rate monitoring					X			
BODPOD‐test		X			X			
PMBC blood draw		X			X	X		
Measurements of handgrip strength		X			X			
MoCA (montreal cognitive assessment)		X			X			
Symbol digit modalities test (SDMT)		X			X			

^*^
In people randomized to the exercise or combined intervention group.

The study was conducted in accordance with good clinical practice guidelines (Declaration of Helsinki, ICH‐GCP), and ethics approval was obtained from the ethics committee of the Medical University of Graz (EK 35‐337 ex 22/23). All participants provide written informed consent prior to participating in the study.

#### Study population

2.2.1

All study participants are aged 18 to 75 years old with established T2D with HbA1c levels ≥7.0% (≥53 mmol/mol) and ≤10.0% (≤86 mmol/mol). They have a BMI >27.0 kg/m^2^ and maintained a stable body weight for the preceding 3 months.

Individuals who are willing and able to comply with study procedures, including the prescribed fasting regime and exercise protocol, are included in the study.

The key exclusion criteria contain any other form of diabetes mellitus than T2D, history of diabetic ketoacidosis, treatment with insulin or sulfonylurea, known active malignancy, pregnancy or any chronic medical condition that could interfere with the interpretation of study outcomes. Additional exclusions include conditions that prevent participation in the exercise programme, acute coronary syndrome or stroke within the last 6 months.

#### Recruitment

2.2.2

People living with overweight and T2D without insulin therapy are recruited from the Diabetes Registry for Biomarker Research Graz, via advertisement in local newspapers, social media platforms like Facebook and pamphlets distributed to general practitioners' surgeries.

#### Randomization

2.2.3

Participants are randomized in a 1:1:1:1 ratio to one of the four intervention groups: Intermittent energy restriction alone, structured exercise alone, combination of intermittent energy restriction and exercise or no‐intervention control group. Randomization is performed using the Randomizer Software (http://www.randomizer.at), according to schedule generated by an independent statistician.

#### Intervention

2.2.4

The active study intervention period is 84 ± 7 days followed by a consolidation period for 21 months to further investigate sustainability of the interventions. All arms are treated according to the Austrian diabetes guidelines,^22^ which are in line with the EASD/ADA consensus statement.^23^
Intermittent energy restriction

Participants of the Intermittent energy restriction group are instructed to consume only 25% of the recommended daily caloric intake (caloric intake is fixed at a maximum of 600 kcal) within a time window of 6 h on fasting days (Monday, Wednesday, Friday) and eat food as desired on alternating feast days (Tuesday, Thursday, Saturday, Sunday). As such, on fast days, participants are fasting for approximately 18 h (6 h eating window on fasting days). Participants of this group receive dietary counselling at baseline.
bExercise group

Participants assigned to the exercise group participate in a moderate‐intensity physical activity program three times a week for 12 weeks. This program comprises an indoor cycling unit, a nordic walking session and a structured body weight aerobic session, all performed at moderate intensity and supervised by a qualified exercise physiologist. All training sessions are monitored by a wrist‐worn fitness tracker (movisens GmbH, Germany). All exercise sessions last 60 min including a 10‐min warm‐up performed at 40–60% of maximum heart rate (HR_max_), followed by a cool‐down phase. Heart rate (HR) during exercise sessions will be recorded using a HR monitor (Polar, Finland).
cCombined exercise and Intermittent energy restriction

Participants in the combined intervention group follow both the IER regime and the exercise program, with exercise sessions scheduled on the IER days.
dControl group

Participants in the control group are instructed to maintain their usual lifestyle habits and not alter their eating or physical activity habits throughout the 12‐week intervention period. No specific lifestyle counselling session is provided to this group.

Participants of all four groups are instructed on how to apply and use the CGM device and how glucose readings and trend arrows are to be interpreted.

### Sample size estimation

2.3

The sample size estimation is based on the analysis of covariance (ANCOVA) approach and data from our INTERFAST‐2 study that investigated exercise and fasting interventions in people with T2D treated with insulin.^24^ Based on INTERFAST‐2 data, we assumed the mean ± standard deviation body weight of 104 ± 13 kg at baseline, correlation (r) of 0.95 from baseline to follow‐up and the mean difference in weight loss of 5.0 ± 4.1 kg from baseline to follow up between intervention arms. Considering a 2‐sided type 2 error rate of 5% and a power of 90%, a total of at least 60 completers is required (15 in each study arm). The study discontinuation rate is expected to be 15%; therefore, the overall sample size is estimated to be 70 participants but could be higher to satisfy the requirement of 15 completers in each study arm.

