## STRENGTHS AND LIMITATIONS /DISCUSSION

3

Weight reduction is one of the cornerstones of T2D therapy in people living with overweight or obesity. Previously we investigated the effects of intermittent energy restriction in people with insulin treated T2D,^24^ demonstrating that 3 non‐consecutive days of IER per week over 12 weeks improved HbA1c, reduced body weight and led to a total daily insulin dose reduction. Physical activity has also been shown to improve glycaemic control^28^ and is therefore recommended in T2D management guidelines all over the world.^15^, ^23^ However, data on potential beneficial effects of combining IER with structured exercise on weight loss and glycaemic control remain scarce.

The greatest strength of this study is its randomized controlled design together with CGM data collected throughout the active intervention phase for all groups, as well as the control group. Besides analysing the glycaemic excursions during fasting and/or exercise with CGM, participants have the possibility to learn how eating habits and exercise affect blood glucose levels. As all groups use CGMs, the effects observed in the IER, exercise and combination groups are controlled for this CGM inherent effect.

A challenge of this study is the evaluation of HbA1c reduction during the active phase, as additional non‐randomized medication including GLP‐1 receptor agonists may be started if HbA1c remains >58 mmol/mol (>7.5%) at visit 3. However, not intensifying the anti‐hyperglycaemic treatment during the active phase was considered unethical. We have defined the change in glucose‐lowering medication (decrease, no change, increase) as secondary outcome to specifically look into this topic and will collect detailed information on changes in metabolically active pharmacological agents. Another limitation is the duration of the active phase of only 12 weeks. However, we perform follow‐up visits up to 2 years after randomization to evaluate whether participants continued to implement the intervention in their daily routine and how sustainable a potential effect observed after the 12‐week active phase was.

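### The 5.0 kg planning difference has an unclear source for exercise versus control, and the stated 90% power holds only for one unadjusted comparison; under the planned Dunnett test it is about 82-83%

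*Protocol article*

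**What the plan says.** Section 2.3 of the protocol article (Sample size estimation) takes its planning values from INTERFAST-2, cited as reference 24 and described as a "study that investigated exercise and fasting interventions in people with T2D treated with insulin". The values are a baseline weight of 104 kg with SD 13 kg, a baseline to follow-up correlation of 0.95, and "the mean difference in weight loss of 5.0 ± 4.1 kg from baseline to follow up between intervention arms". The contrast to which this difference belongs is not named. The error rates are given as a "type 2 error rate of 5% and a power of 90"%, and the result is 15 completers per arm, 60 in all.

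Section 3 (Strengths and limitations / Discussion) cites the same reference 24 with other words: "Previously we investigated the effects of intermittent energy restriction in people with insulin treated T2D". The findings it reports are that "3 non‐consecutive days of IER per week over 12 weeks improved HbA1c, reduced body weight" and "led to a total daily insulin dose reduction". The sentence that then turns to physical activity cites a different reference and concerns glycaemic control, not weight.

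Section 2.8 (Statistics) compares each of the three active arms with control in step 1, at two-sided alpha 0.05 with Dunnett adjustment. Exercise versus control is one of these three. Section 2.2.4 describes the exercise arm as a moderate-intensity "physical activity program three times a week for 12 weeks". No expected weight effect of that programme is given anywhere.

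**The concern.** Two things in the sample size paragraph do not fit the rest of the article.

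First, the source. If INTERFAST-2 had an exercise component, 5.0 kg could in principle bear on any of the arms. If the Discussion's account is complete, 5.0 kg is an IER effect, and nothing in the article supports it for exercise alone. In either case one value cannot describe every pair of arms: if IER and exercise each beat control by 5.0 kg, they do not differ from each other. The source participants also used insulin, whereas insulin treatment is an exclusion criterion here.

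Second, the test. The power is stated without reference to the Dunnett adjustment that the Statistics section prescribes.

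The trial asks which of three strategies is best suited to reducing weight. A reader who takes 90% power to apply to each comparison with control may read a non-significant exercise result as evidence that exercise does not work, when the comparison may have had much less power than stated.

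**Working it through.** **Inputs.** From section 2.3: difference 5.0 kg, SD 4.1 kg, baseline SD 13 kg, correlation 0.95, 15 completers per arm. From section 2.8: three comparisons with control, two-sided alpha 0.05, Dunnett. Assumed here: true effects below 5.0 kg for exercise, because the article gives none. The calculation is for completers, with a common residual SD and one baseline covariate.

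**Step 1, the SD.** The ANCOVA residual SD is 13 × √(1 − 0.95²) = 4.06 kg. The SD of change is 13 × √(2 × (1 − 0.95)) = 4.11 kg. Both agree with the stated 4.1 kg.

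**Step 2, reproduce the stated figure.** The standard error of a difference between two arms is 4.1 × √(2/15) = 1.50 kg, so the noncentrality at 5.0 kg is 5.0/1.497 = 3.34. A single two-sided t test at 5% with 28 df has power 89.7% (90.2% with SD 4.06). The stated 15 per arm and 90% are reproduced, as one unadjusted comparison.

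**Step 3, the printed error rate.** Power of 90% is a type 2 error of 10%, so a type 2 rate of 5% contradicts it. With SD 4.1 kg, a type 2 error of 5% would need 19 per arm (power 95.5%; 18 per arm gives 94.5%). The stated 15 per arm fits only if the 5% is the type 1 error rate.

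**Step 4, power under the planned test.** The two-sided Dunnett critical value for three comparisons with control and 60 − 5 = 55 df, found by simulation, is 2.415. The power comes from the noncentral t distribution with this critical value, 15 per arm and SD 4.1 kg. The unadjusted column uses 28 df.

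| True difference from control | One unadjusted test | Dunnett |
|---|---|---|
| 5.0 kg (article's value) | 90% | 82% |
| 4.0 kg (assumed) | 73% | 60% |
| 3.0 kg (assumed) | 49% | 35% |
| 2.5 kg (assumed) | 36% | 24% |
| 2.0 kg (assumed) | 25% | 15% |

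With SD 4.06 kg the Dunnett power at 5.0 kg is 83%.

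**Step 5, precision.** The half-width of the Dunnett interval is 2.415 × 1.497 = 3.6 kg.

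**Step 6, the two descriptions of reference 24.** Section 2.3 names exercise and fasting. Section 3 names IER, and every result it reports is an IER result. Section 3 neither mentions nor rules out an exercise component. The article does not settle which account is complete.

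**The case against.** The strongest reply is that section 2.3 does state a basis: a study of exercise and fasting. The Discussion reports one result of that study and does not say that IER was all it tested. This stands. A reader might infer that INTERFAST-2 had no exercise component, so that 5.0 kg must be an IER-versus-control difference. The documents do not support that step, because only the cited source can settle it.

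A reader might also infer that exercise versus control has power of only 15-35%. That range follows if exercise alone yields about 2-3 kg and Dunnett is applied, but the article states no such effect. An energy-balance estimate of the likely loss would need metabolic costs and a conversion from energy to weight that are not in the article either. At the article's own 5.0 kg, power is 90% unadjusted and 82% with Dunnett. The lower figures can stand only as conditional values.

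A third tempting reading is that the source's weight loss depended on the fall in insulin dose. The article lists the two as separate results and does not link them.

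It is also fair to say that section 2.3 never names exercise versus control as 90% powered, that the error-rate slip is evident from context since section 2.8 gives the alpha, and that the planned adjusted intervals will show any imprecision. These points limit the harm. They do not reconcile the two descriptions, identify the contrast, or bring the power under the planned test up to 90%.

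**Conclusion.** The point holds as one of internal consistency and justification. The sample size arithmetic itself is sound for one unadjusted test.

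- Sections 2.3 and 3 describe the same reference differently, so the basis for applying 5.0 kg to exercise versus control is unclear.
- On the article's own inputs, power per comparison with control is about 82-83% under the planned Dunnett test, 7 to 8 percentage points below the stated 90%. This assumes 15 completers per arm and an SD of 4.06-4.1 kg.
- Power for exercise versus control depends on an effect that the article does not give. It is about 60% at 4 kg, 35% at 3 kg and 15% at 2 kg.
- The printed type 2 error rate of 5% is wrong beside 90% power.

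**What to change.** No change in sample size is asked for.

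1. Reconcile the two descriptions of INTERFAST-2 in sections 2.3 and 3, and state which contrast in that study the 5.0 kg refers to.
2. Restate the power as about 82-83% per comparison with control under Dunnett at 5.0 kg, and limit that claim to the contrasts that the source supports.
3. Give the power for exercise versus control as a conditional range with its assumed effects (for example 82% at 5 kg, 60% at 4 kg, 35% at 3 kg, 15% at 2 kg). State that a non-significant exercise contrast will be reported as inconclusive, with its interval, whose expected half-width is about 3.6 kg.
4. Replace type 2 by type 1 for the 5% error rate in section 2.3, in line with the two-sided alpha of 0.05 in section 2.8.

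The cost is wording. The article says that the statistical analysis plan will be finalized before database lock, so the changes can be made there although 65 participants had been randomized by November 2025. The price is a stated power that looks less favourable, possibly much less so for the exercise arm.

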### Outcomes

2.4

The primary outcome of this study is the change in body weight from baseline to end of the intervention phase (i.e., 12 weeks). Key secondary outcomes comprise change in Time In Range (TIR) [70─180 mg/dL; 3.9─10.0 mmol/L] from baseline to end of intervention and change in the composite of improvement in TIR of at least 5%, weight reduction of at least 3% and stable or reduced glucose‐lowering treatment at end of intervention. Safety endpoints include difference in the number of severe adverse events and differences in TBR1 [54─<70 mg/dL; 3.0─<3.9 mmol/L] and TBR2 [<54 mg/dL; <3.0 mmol/L].

The full list of exploratory secondary outcomes can be found in Table S1.

### Investigations

2.5

#### Medical history

2.5.1

A medical history is recorded at screening visit to capture illnesses, disorders and medications. This information is updated on all follow‐up visits. Body weight, height and blood pressure are measured at all visits.

